### Sampling strategy

Households will be selected using a hybrid sampling technique to obtain as random of a sample as is feasible. Because a truly random sample would be logistically infeasible due to expense and lack of a household-level sampling frame, a hybrid systematic and random sampling technique will be used. To accomplish this, a modified procedure based on the World Health Organization Expanded Programme of Immunization (EPI) method will be used [10,11]. First, each area will be split into 127 grid squares using Geographic Information System (GIS) technology. The center point of each grid cell will then be generated using GIS. This is the starting location for the enumerators for each day’s survey. GPS will be used to navigate to the precise starting location each morning.

After arrival at the center point, the spin-the-bottle technique will be used [10]. Each enumerator team will be supplied with a random direction by spinning a pen or bottle. On arrival to the center of the grid cell, they will travel in the given direction surveying houses along the line given by the direction.

As many of Lwala’s programs and outcomes of interest focus around maternal and child health, households with children under five years of age will be oversampled. At least five of seven surveys administered in each grid square will be administered to households with children under five years. If the enumerator reaches the end of the grid cell before surveying both seven total households and five households with a child under five years, they will walk along the edge of the grid to the closest corner to find more households.

This approach minimizes the biases of the traditional spin-the-bottle sampling method [12] by using the center of an arbitrary square in place of the center of a town or gathering area.

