## Methods

### Study design

This is a repeated, cross-sectional survey allowing for longitudinal analyses of population and community-level metrics related to health, education, and socioeconomics. Households will be selected for surveying in areas currently receiving Lwala programming and in areas planned to receive Lwala programming in the future. Nearby geographic regions with no planned Lwala services will be surveyed and serve as comparison locations. Subsequent surveys will provide new cross-sectional data for a given geographic area by randomly selecting households for interview utilizing the same sampling strategy; however, it will not specifically target the same households for future surveying. Data collection will begin in 2021 and occur every three years until 2027. Previous surveys have been conducted in 2017 and 2019.

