### Enumerator selection, training, and team composition

Surveys will be administered in the household by trained enumerators who are not regular Lwala staff. All enumerators will be hired from the community. Enumerators will be selected from a pool of college graduates or equivalent experience, with preference given to those with experience in survey administration, Dholuo fluency, and high performance in training.

Prior to survey implementation, the enumerators will participate in a five-day training intended to familiarize them with the survey questions and tablet platform, the methodology for household and respondent selection, and recommendations for dealing with potential challenges in the field. Training will focus on the responsible conduct of research, an understanding of the intent of the survey questions, the appropriate translation options in Dholuo, the appropriate skipping of questions according to survey logic, and the procedure for marking responses based on the question type. Enumerators that show signs that indicate the inability to interact appropriately with interviewees or generally do not perform well will be dismissed before field data collection begins.

Data collection teams will consist of a team leader and two enumerators. The team leader will assist in household identification and survey consent while enumerators are completing surveys with eligible households. An overall survey supervisor will also be present to assist with problems that arise and conduct spot checks by observing surveys.

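### The walking direction, the only random step described in household selection, is a bottle spin made on site with no pre-generated or recorded bearing stated

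*Protocol article*

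**What the plan says.** The Sampling strategy section of the protocol article lays out the procedure in order.

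- Squares: "each area will be split into 127 grid squares using Geographic Information System (GIS) technology".
- Starting point: "The center point of each grid cell will then be generated using GIS". Teams reach it by GPS.
- Direction: "After arrival at the center point, the spin-the-bottle technique will be used", and "Each enumerator team will be supplied with a random direction by spinning a pen or bottle".
- Households: "they will travel in the given direction surveying houses along the line given by the direction".
- Top-up when the line runs out: "they will walk along the edge of the grid to the closest corner to find more households".
- Quota: seven households per square, at least five of them with a child under five.

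The section says that full random sampling is not practicable, for reasons of cost and because no household list exists. Its aim is to come as close to random as it can. It claims to reduce the known biases of the bottle method by starting from the centre of an arbitrary square instead of a town centre.

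The recruitment section adds that a house with no head present is passed over for the next on the line, with a later return if possible. The Study design section says later rounds will work by "randomly selecting households for interview utilizing the same sampling strategy". On staffing: "All enumerators will be hired from the community". The same section says enumerators are not regular Lwala staff.

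**The concern.** Wards are not randomised. Within a ward, the squares and centres are fixed, and so are the rules that follow the spin. Whatever randomness the household sample has comes from the direction.

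That direction is produced by a physical spin at a moment when paths, slopes and visible houses are known and a quota is waiting. A spin toward an empty field means a longer day, and a second spin takes seconds. The article names no bearing fixed in advance against which the line walked could be compared.

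If teams drift toward visible, accessible houses, clustered households are over-represented. Access to roads and facilities plausibly relates to skilled delivery, immunisation and antenatal care, which are among the primary outcomes. For a single-round ward estimate this is a direct bias, and a larger sample does not shrink it. For objectives 2 and 3 (change over time, and programme against comparison areas) it matters only if the degree of steering differs between rounds or wards.

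**Working it through.** **1. The plan's own figures.** Comparing 50% with 60%, two-sided 5%, 80% power, no continuity correction gives 388 per group. 388 x 1.6 = 620.8, so 621. Allowing for 30% loss, 621 / 0.7 = 887.1, stated as 887. 8 x 887 = 7,096. All reproduce, and none depends on how the direction is generated.

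**2. Is the spin the only random step?** 127 squares x 7 households = 889, against a target of 887. Every square is therefore needed and none is drawn at random. The centre is fixed by GIS. After the spin, the article gives only fixed or convenience rules: houses along the line, edge to the closest corner, the under-five quota, and the absent-head skip. So yes, among the steps described.

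**3. Does the mitigation reach the direction?** Replacing a town centre with a square's centre changes where the line begins. It has no bearing on how its direction is chosen.

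**4. The incentive.** Study population section: North Kamagambo covers 46.4 km², county density is 427 persons per km², household size is 4.6.

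- Square area: 46.4 / 127 = 0.365 km², side about 604 m.
- Households per square: 0.365 x 427 / 4.6 = about 34.

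This pairs one ward's area with a county average, so it does not describe the other seven wards.

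The rest is simulated under assumptions not in the documents: 30-50% of the 34 households lie in one cluster (SD 70 m) placed at random; the team meets houses within 25 or 50 m of the line; and a re-spinning team keeps the direction with the most houses.

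| Strip half-width | Houses met, one spin | Best of two |
|---|---|---|
| 25 m | about 1.6-1.7 | about 2.3-2.6 |
| 50 m | about 2.8-3.2 | about 3.9-4.2 |

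Seven are needed, so a re-spin saves real work. Equally, on an honest spin about four to five of the seven interviews come from the top-up.

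**5. Size of the bias.** Counting all seven interviews, with the edge walk modelled and any remainder filled evenly from the square:

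| Re-spinning in every square | Rise in cluster's share of interviews | Ward shift if the outcome differs by 20 points |
|---|---|---|
| Best of two | about 1-4 points | about 0.2-0.7 points |
| Best of three | about 2-7 points | about 0.5-1.4 points |

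If only 10-20% of squares were re-spun, the shift runs from 0.10 x 0.2 = 0.02 to 0.20 x 1.4 = 0.28 points.

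**6. Yardsticks.** The planned detectable difference is 10 points. The standard error of a between-round difference at 621 per round and design effect 1.6 is sqrt(2 x 0.25 x 1.6 / 621) = 0.036, or 3.6 points. Even the extreme scenario is under half of one standard error.

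**The case against.** The strongest reply is that this is a condensed article. Whether the direction is logged belongs in a field manual, and the article does describe training in household selection, a team leader with each team, a supervisor in the field, daily logs and nightly review. It also adapts a recognised survey method and admits the compromise.

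Much of that stands. Three stronger readings are tempting and are not supported.

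- **No record is kept.** The article is silent on this. It is true that none of the oversight described is said to cover the direction, but silence is not a statement that it cannot be audited.
- **An unblinded field team makes the spin and may favour programme wards.** The wording is passive and names no spinner. Blinding is not mentioned, enumerators are not regular Lwala staff, and no motive to favour one type of ward is shown.
- **The ward estimate shifts by 1-2 points.** Applying the 20-point gap to first-line interviews alone gives a figure of that order. It assumes that every square is re-spun and leaves out the edge-walk top-up.

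The reply does not dispose of the point. The on-site spin is what the article prescribes, and a bearing fixed beforehand is a different procedure. A logged spin would still not show spins discarded before logging. The reasons given against full random sampling (cost, no household list) do not apply to a bearing, which needs neither a list nor extra visits.

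**Conclusion.** The point holds in a limited form. The only random step described in household selection is left to a spin made in the field by or in front of people with a quota to fill, and the article states no pre-generated or recorded direction. Its mitigation covers the starting point alone.

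The magnitude is unknown. On the assumptions above it is roughly 0.2-1.4 points per ward estimate if every square were re-spun, and about 0.3 points or less if 10-20% were. It reaches the change and programme-versus-comparison analyses only through differences in steering between rounds or wards, which nothing in the documents allows one to estimate. The article does not claim a truly random sample, so this is no contradiction and changes no sample size. It is an inexpensive improvement, lying between optional and recommended, and is worth making because the same strategy is to be reused in 2024 and 2027.

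**What to change.** In the Sampling strategy section, replace the pen or bottle spin with wording such as: for each grid square and each survey round, a random bearing (0-359 degrees) is generated centrally together with the centre point and is released to the team's device on arrival; the GPS position of each interviewed household is recorded, and the nightly data review compares these positions with the assigned line.

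Cost: one extra column in the GIS output and one added check in a review that already takes place, with no extra staff, visits or households. Teams must follow a compass or GPS bearing and lose the freedom to avoid an awkward direction. If a round has already been fielded with the spin, the change of method should be documented so that comparisons across rounds can take it into account.

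The change protects the first-line direction only. The edge-walk top-up, the under-five quota and the absent-head substitution remain non-random and should still be described as such.

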**Fig 2 pone.0256555.g002:**
[figure not shown]
Lwala Community Alliance theory of change. Lwala utilizes a community-led model to improve health, education, and economic outcomes.

Lwala’s efforts in North Kamagambo have led to significant successes in several key health metrics, including being on track to outpace Millennium and Sustainable Development Goal (SDG) targets for childhood mortality, attaining an under-five mortality rate of 29.5 per 1,000 live births as of 2017 [3] compared to the SDG target of under 25 deaths per 1,000 live births by 2030 [4]. This success has led to local health authorities inviting Lwala to expand its CHW model into nearby East and South Kamagambo wards, as well as to begin providing technical assistance toward improved health service delivery in the government-supported health facilities of these wards. Along with service expansion has come the effort to systematically and academically evaluate health metrics and changes in outcomes in the community. This led to multiple iterations of a community-wide household survey in Lwala’s original catchment area and subsequently in the expansion areas [3,5,6]. We now aim to conduct repeated cross-sectional surveys to evaluate the effect of Lwala’s programming over time and characterize health metrics in the area.

Here we describe the Lwala Household Survey (LHS) with the following objectives: (1) to assess the health, socioeconomic, and education status of current and future communities receiving programming from Lwala; (2) to measure changes in these metrics over time in the presence of Lwala programming; (3) to compare changes over time in key metrics to determine the effect of Lwala presence and programming.

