### Sample size

The study has a wide range of indicators of interest, including child mortality, skilled delivery rate, vaccination coverage, contraceptive prevalence, and antenatal care. These metrics vary in their community prevalence and would thus require different sample sizes. For example, under-five mortality is relatively rare at 82 per 1,000 live births while full vaccination is relatively common at 57.2% of children [1]. A community prevalence of 50%, yielding maximum variation and therefore maximum sample size, was used to adequately power all metrics. Within each area, the sample size was calculated to detect a 10% difference over time using a power of 80%, precision of 0.05, and design effect of 1.6. Design effect was calculated according to the equation:
DE=(1+(m−1))*ICC
where DE is the design effect, m is the number of the household to be sampled per cluster, and ICC is the inter-cluster correlation. An ICC of 0.15 was used based on international standards [9]. This would require a sample of 621 households in each area. This estimate was inflated by 30% to give a total goal sample of 887 per area. For the first survey, which includes eight areas, the total sample size will be 7,096 households. Subsequent surveys will include the same number of households per area. Table 2 below shows the sample size for each ward.

**Table 2 pone.0256555.t002:** Sample sizes for successive surveys.

	Minimum	Maximum	Number of clusters	Households with children	Additional Households	Total per Cluster
North Kamagambo	621	887	127	5	2	7
East Kamagambo	621	887	127	5	2	7
Central Kamagambo	621	887	127	5	2	7
South Kamagambo	621	887	127	5	2	7
North Sakwa	621	887	127	5	2	7
Central Sakwa	621	887	127	5	2	7
Central Kanyamkago	621	887	127	5	2	7
West Kanyamkago	621	887	127	5	2	7

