### Survey instrument

The survey tool contains over 300 questions and is based on several different validated tools (Table 3). The full survey is available in the supplemental materials (S1 Appendix). The survey is designed to capture metrics across 13 public health modules in a reproducible manner. The estimated time to complete one interview is 45 minutes.

**Table 3 pone.0256555.t003:** Survey modules, key metrics, and sample sizes.

Survey Section	Question Sources	Key Metrics
Personal Demographics	Kenya Demographic and Health Survey [1]	Age Marital status
Household Information	Kenya Demographic and Health Survey [1]	Household census Birth history (child mortality) Total fertility rate
Economics	Kenya Demographic and Health Survey [1] Poverty Probability Index [13]	Poverty probability Multidimensional poverty index Income
Family Planning	Kenya Demographic and Health Survey [1] Condom Use Self-Efficacy Scale [14]	Contraceptive prevalence rate Unmet need for contraception
Child Health	Kenya Demographic and Health Survey [1]	Antenatal care visits Careseeking for childhood illness
Nutrition	WHO Infant and Young Child Feeding [15] Household Hunger Scale [16]	Ever breastfed Exclusive breastfeeding Minimum acceptable diet Household hunger
Vaccinations	Kenya Demographic and Health Survey [1]	Complete vaccination rate
HIV	Kenya Demographic and Health Survey [1] van Rie Stigma Scale [17–19]	HIV testing rate HIV stigma
Water and Sanitation	Kenya Demographic and Health Survey [1]	Drinking water source Previous sanitation training
Education	Kenya Demographic and Health Survey [1]	School attendance Educational attainment
Interpersonal Violence	Kenya Demographic and Health Survey [1] Abuse Assessment Screen [20] Partner Violence Screen [21]	Interpersonal violence prevalence
Mental Health	Patient Health Questionnaire (PHQ-8) [22,23]	Depressive symptom prevalence
Programming	Lwala monitoring and evaluation tools	Service access Service satisfaction
Observational	Kenya Demographic and Health Survey [1]	Mosquito net use Handwashing facility Latrine type
COVID-19	WHO COVID Survey Tool and Guidance [24] van Rie Stigma Scale (adapted) [17–19]	Personal COVID-19 experience Prevention behaviors Testing and vaccination perceptions COVID-19 stigma

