### Participant recruitment and enrollment procedures

Upon arrival to a selected household, the enumerator will first ask to speak to the head of the household. If the head of household is present, the enumerator will then ask if they have children under 5 years old living in the household. If no head of household is present, the enumerator will skip this house, going to the next household along the line selected. They will return to the household later if the head of household is returning home. We define a household as a group of people that eat under the same roof that have lived in the same dwelling for the past year. This excludes temporary visitors.

Heads of households that are 18 years of age or older will be surveyed. Female heads of household are preferred as female family planning, interpersonal violence, and child health and nutrition are key survey areas. Male heads of household will only be surveyed if female heads are unavailable. The only other inclusion criteria will be living in a household in one of the surveyed communities. Households with children under five years of age will be oversampled. Participants will receive 50 KES (about $0.50) in airtime for their participation.

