### Data analysis

After administration, data will be exported to the latest version of Stata (StataCorp LP, College Station, TX) for further analysis. Initial analyses will focus on descriptive statistics of health, socioeconomic, and education metrics in the sample population across areas. Further analyses will characterize these metrics in terms of demographic variables and compare these metrics to county and national averages using appropriate statistical tests, including chi-squared tests, t-tests, ANOVA, and non-parametric tests. These analyses will be conducted following each survey in 2021, 2024, and 2027.

Analysis of outcome metrics will be conducted using multivariable linear regression, logistic regression, and generalized estimating equations. Specific primary outcomes of interest include under-five mortality, immunization rate, skilled delivery rate, contraceptive prevalence rate, and antenatal care visits. Longitudinal analyses will be performed at the end of the study in 2027 once multiple timepoints are available. Interim longitudinal analyses will also be performed following each survey administration. Trends in outcomes and potential effects of programs will be assessed. This will involve interrupted time series techniques with a segmented regression to asses intervention effects over repeated observations.

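### The quota for households with a living under-five selects on child survival, so an unweighted under-five mortality estimate is biased low wherever the quota binds

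*Protocol article*

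**What the plan says.** All references are to the protocol article.

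- **Sampling strategy:** because of the maternal and child health focus, "households with children under five years of age will be oversampled". The rule per grid square is "At least five of seven surveys administered in each grid square will be administered to households with children under five years". Table 2 shows the same split, five plus two, in all eight wards.
- **Participant recruitment and enrollment procedures:** when the head of household is present, "the enumerator will then ask if they have children under 5 years old living in the household". Group membership is thus set by children alive and resident at the visit.
- **Survey instrument, Table 3:** child mortality is derived from the birth history in the household module. No look-back window is given.
- **Data analysis:** "Specific primary outcomes of interest include under-five mortality, immunization rate, skilled delivery rate, contraceptive prevalence rate, and antenatal care visits". The methods named are linear and logistic regression, generalized estimating equations and segmented regression.

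The article does not describe a count of households passed over by group. The Limitations section does not mention selection on survival.

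**The concern.** Oversampling on a characteristic does no harm if that characteristic is unrelated to the outcome, or if the analysis undoes it. Here it is related by construction. A child who dies cannot place the household in the favoured group. If that child was the only one under five, the household moves to the group limited to two of seven interviews. Deaths in such households are under-represented relative to births in households with a surviving young child.

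Two things are at stake. The first is the level: the Introduction sets a North Kamagambo rate of 29.5 per 1,000 against a target of under 25, so a modest proportional error matters. The second is comparison. The bias depends on how common under-five households are, and that may differ between wards and change over rounds, while objective (3) is to compare changes over time.

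**Working it through.** **Printed figures.** The plan gives no figure for this bias, and its sample size is not in dispute: 388 × 1.6 = 620.8, rounded to 621, and 621 / 0.7 = 887.1, printed as 887.

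**Inputs from the protocol.** Five of seven interviews in households with a living under-five (s = 5/7). True rate q = 0.082, from Sample size: "under-five mortality is relatively rare at 82 per 1,000 live births".

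**Assumptions, not in the protocol.** One mother per household, 0 to 3 births in the last five years with proportions p0 to p3, independent deaths, and an unweighted ratio of deaths to births over those five years.

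**Formulas, per household.**
- Share with a living under-five: P = 1 − Σ p_k q^k
- All births: B = Σ k p_k. All deaths: D = qB
- Births in households with no living under-five, all of them deaths: D0 = Σ k p_k q^k
- Relative sampling weights: w1 = s/P with a living under-five, w0 = (1 − s)/(1 − P) without
- Unweighted estimate: [w1(D − D0) + w0 D0] / [w1(B − D0) + w0 D0]

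**One case in full**, births 35/38/23/4%:
- P = 1 − (0.35 + 0.03116 + 0.00155 + 0.00002) = 0.617
- B = 0.96, D = 0.07872
- D0 = 0.03116 + 0.00309 + 0.00007 = 0.03432, which is 44% of all deaths
- w1 = 0.7143/0.6173 = 1.157, w0 = 0.2857/0.3827 = 0.747
- Deaths: 1.157 × 0.04440 + 0.747 × 0.03432 = 0.0770
- Births: 1.157 × 0.92568 + 0.747 × 0.03432 = 1.0968
- Estimate: 0.0770/1.0968 = 70 per 1,000, against a true 82

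**Across assumed birth distributions, true rate 82:**

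| Births 0/1/2/3 (%) | Share P | Deaths in households with no living under-five | Estimate, exactly 5 + 2 | Estimate, cap of two |
|---|---|---|---|---|
| 30/35/27/8 | 67% | 35% | 77 (−6%) | 72 |
| 35/38/23/4 | 62% | 44% | 70 (−14%) | 67 |
| 45/37/16/2 | 52% | 53% | 59 (−28%) | 58 |
| 50/35/13/2 | 47% | 55% | 54 (−34%) | 54 |

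The last column reads the rule as a floor in each grid square: households are taken in order, with at most two lacking an under-five. The expected number lacking one is then 2 − 2P^7 − 7(1 − P)P^6. At P = 0.617 this is 1.78, so s = 1 − 1.78/7 = 0.745 instead of 0.714.

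**Effect of the birth window.** A second simulation followed reproductive histories, with and without a shortened birth interval after a death and with and without clustering of deaths. At shares of 42% to 59%, the ratio of unweighted to true rate was 0.55 to 0.86 for births in the last five years and 0.83 to 0.96 for all births. At shares of 71% to 74%, with exactly five of seven, it was 0.98 to 1.06.

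**Lower-mortality setting.** With a true rate of 29.5 ("attaining an under-five mortality rate of 29.5 per 1,000 live births as of 2017"), the five-year calculation at assumed shares of 38% to 69% gives about 18 to 28 per 1,000. That range contains the target of 25.

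**Weighting.** Setting each group back to its true share makes w1 = w0, and the estimate returns to D/B = q, because households without a living under-five are still sampled.

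**The case against.** **Weights may be planned elsewhere.** Data analysis is two paragraphs of a journal article, and survey weights are commonly left to an analysis plan. This stands. A reader might infer that mortality will be analysed unweighted, but the article does not say so. The point is that the stated quota makes weights necessary.

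**The data for weights may exist.** The door question is already asked wherever a head of household is present, and the electronic forms are not shown. An outside source might also give ward-level shares. So a reader might infer that weights could never be rebuilt, but the documents support only that no count of passed-over households is described. The interviewed sample cannot supply the share, because the quota largely sets it.

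**The larger figures rest on a narrow window.** This stands. Five years is the window most closely tied to having a living under-five, and Table 3 does not restrict the birth history to it. Counting all births dilutes the bias but does not remove it while oversampling occurs.

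**The quota may not bind everywhere.** This stands in part. With exactly five of seven, the bias vanishes or slightly reverses once the natural share reaches about 5/7. If the rule caps the other group at two in each square, some squares hit the cap even at that share. The size in any ward is unknown.

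**The same quota applies in all eight wards.** Where shares are similar, the proportional bias is largely common and cancels in ratio comparisons. This stands.

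Oversampling itself is reasonable for child-health outcomes, and nothing here argues against it.

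**Conclusion.** The point holds in conditional form. Sampling on a living under-five makes inclusion depend on child survival, and where the quota binds, an unweighted under-five mortality estimate is biased low. Under assumed shares of 47% to 67%, births in the last five years and exactly five of seven, a true 82 per 1,000 is estimated at about 54 to 77 (6% to 34% low). Counting all births gives about 4% to 17% in the second simulation. The shares, birth distributions and window are assumptions.

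Two stronger readings are not supported. A reader might infer that mortality is understated in every ward, but that depends on local shares the documents do not give. A reader might also infer that the bias favours the programme: a fall in the share from 62% to 52% at constant mortality would move the estimate from 70 to 59, a spurious drop of 16%. That requires the share to fall more in programme wards than in Uriri, and no such trend is reported. What can be said is that the bias may not fully cancel between wards or rounds if fertility changes differ.

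The demonstration covers one of five primary outcomes. It is best treated as a cheap improvement.

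**What to change.** 1. Record on the tablet the answer to the existing door question for every household approached, including those passed over because the quota is full. Mark households with no head present separately.
2. State that mortality and other birth-history estimates are weighted by the inverse of the stratum sampling fraction (interviewed over approached) in each ward or grid cell. Ward-level fractions will be steadier, since a cell holds only seven interviews.
3. State the birth window used for under-five mortality.

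Alternatively, define the oversampled group by any birth in the last five years, living or dead. Every birth in that window then falls in one group, and this selection no longer acts on a five-year estimate. The door question would then have to cover children who have died.

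The cost is one extra field and slightly larger standard errors from weighting. The count should be in place before each round, because households passed over cannot be counted from the interview data afterwards.
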